**(1)** **Pre-treatment events (PTE)**

PTE is defined as any adverse medical event that occurs prior to administration of any study drug in a subject who has signed informed consent, but which does not necessarily have to have a causality to the study.

Concomitant diseases and corresponding complications/abnormalities, new abnormalities that occur during the baseline evaluation are recorded as PTE. If PTEs aggravate abnormally after study drug treatment, investigator is responsible for determining whether it is an AE.

**(2) AEs**

AE is defined as any untoward medical occurrence in a subject who received study drugs, but which does not necessarily have to have a causality to treatment.

**(3) Observation and recording of AEs**

Any medical events that occurred from starting treatment until 28 days after the end of the study drug or the initiation of other anti-tumor therapy, regardless of its causality to study drugs, are considered to be an AE.

If laboratory abnormalities were part of a syndrome, the syndrome or diagnostic finding (e.g., anemia) rather than the laboratory finding (i.e., decreased hemoglobin) will be recorded.

The following information about AEs should be recorded, including time of AE occurrence (starting time) and recovery time (ending time), severity, the causality of AEs to study drugs, follow-up, outcomes, and managements.

AEs are followed-up until the disease is stable, normalized, and returned to baseline.

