**Study Procedures**

| **Visit** | **Screening[1]** | | **Treatment period** | | | | **Post-treatment** | | | **Follow-up of survival** | | |
| --- | --- | --- | --- | --- | --- | --- | --- | --- | --- | --- | --- | --- |
|  |  |  |  |  |  |  | **Withdrawal** | **End-of-**  **treatment** | **Before progression[2]** | | **After progression** | **After DCO[3]** |
|  | 1 | 2 | 3 | 4 | 5+ | 6+[4] | NA | NA | NA | | NA | NA |
| **Visit windows** | -28-0 | -7-0 | ±3 | ±3 | ±3 | ±3 | ±3 | ±3 | ±7 | | ±7 | ±7 |
| **Treatment cycles** | NA | NA | C1D7 | C1D21 | C3D21 | C5D21+ | NA | NA | NA | | NA | NA |
| **Study weeks** | -4-0 | -1-0 | 1 | 3 | 9 | 15+ | NA | With 21 days after treatment discontinuation | Every 6 weeks | | Every 6 weeks | Every 8 weeks |
| **Baseline characteristics** | | | | | | | | | | | | |
| **Informed consent** | X |  |  |  |  |  |  |  |  | |  |  |
| **Demographics** | X |  |  |  |  |  |  |  |  | |  |  |
| **Inclusion/exclusion criteria** | X |  |  |  |  |  |  |  |  | |  |  |
| **Enrollment ID** |  | X |  |  |  |  |  |  |  | |  |  |
| **Physical examination [5]** |  | X | X | X | X | X | X |  |  | |  |  |
| **Vital signs [6]** |  | X | X | X | X | X | X |  |  | |  |  |
| **Medical history [7]** | X |  |  |  |  |  |  |  |  | |  |  |
| **Compliance before enrollment [8]** |  | X |  |  |  |  |  |  |  | |  |  |
| **Radiographic evidence of progression** | X |  |  |  |  |  |  |  |  | |  |  |
| **Laboratory evaluations** | | | | | | | | | | | | |
| **Hemanalysis [9]** |  | X | X | X | X | X | X | X |  | |  |  |
| **Urinalysis [10]** |  | X | X | X | X | X | X | X |  | |  |  |
| **Stool tests [11]** |  | X | X | X | X | X | X |  |  | |  |  |
| **Blood biochemistry [12]** |  | X | X | X | X | X | X | X |  | |  |  |
| **Coagulation function [13]** |  | X | X | X | X | X | X |  |  | |  |  |
| **Thyroid function [14]** |  | X | X | X | X | X | X |  |  | |  |  |
| **Tumor marker** |  | X | X | X | X | X | X |  |  | |  |  |
| **12-ECG [15]** |  | X | X | X | X | X | X |  |  | |  |  |
| **Myo-cardial enzymonram [16]** |  | X |  |  |  |  |  |  |  | |  |  |
| **Echocardiography [17]** |  | X |  |  |  |  | X |  |  | |  |  |
| **Hepatitis B, Hepatitis C, HIV [18]** | X |  | | | | | | | | | | |
| **Pregnancy test [19]** |  | X |  |  |  |  | X |  |  | |  |  |
| **Imaging assessment** | | | | | | | | | | | | |
| **Imaging assessment [20]** |  | X |  | X | At the end of every two cycles (6 weeks ±7 days) | | X |  | X | |  |  |

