20. Imaging assessment: Including CT or MRI of the chest, abdomen, pelvis, and head. Baseline assessment of screening period tumors can be extended to within 3 weeks before treatment, and CT/MRI scans obtained before signing informed consent can be used for screening period tumor assessment if they meet the criteria; bone scans are required if suspected bone metastasis; no symptoms of cerebral hemorrhage need to be confirmed within 28 days before treatment in patients with stable brain metastases.

The imaging examination should be performed on chest and abdominal lesions under the same conditions as the baseline (layer thickness of the scan, use of contrast agents, etc.) on C1D7 and days 21 of every odd numbered cycle; Other lesions identified at baseline or new lesions suspected subsequently should also be examined at the appropriate time. Subjects should be promptly imaged when outgroup for any reason;

The window of the imaging schedule is ±7 days. An unplanned imaging examination may be performed when disease progression (e.g., symptoms worsening) is suspected. Subjects who discontinue treatment for reasons other than imaging-confirmed disease progression should perform an image evaluation at the date of end-of-treatment, and tumor efficacy evaluations are performed every 8-week follow-up thereafter until confirmed disease progression or initiating new tumor treatment is initiated.

1. Examination of brain lesions: Brain MRI and neurological function tests [19];
2. Blood pressure is measured by the subject himself/herself and recorded in the patient diary card. Blood pressure is tested at least 3 times per week for the first 2 cycles and followed up each day if the blood pressure is abnormal. In addition, blood pressure is measured again by the investigator at each follow-up visit, coffee, and tobacco intake are prohibited within 30 minutes before each blood pressure is measured. The measurement of blood pressure is taken in the sitting position with the arm at heart level after at least 10 minutes of quiet sitting, and each blood pressure measurement is taken on the same side;
3. AEs are recorded from the first dose of the study drug until at least 21 days after the last dose and follow-up until the AEs resolved or stabilized;
4. PD-L1 expression: Biopsy tissues are obtained from appropriate subjects for PD-L1 expression using immunohistochemistry.

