1.2.3.4 Pharmacokinetic results

Currently, blood drug concentrations have been measured for the first six dose groups. Following intravenous administration of the drug, the results for serum drug exposure and Cmax indicate good linearity from 3 mg/kg to 30 mg/kg, with a half-life of approximately 320 hours for the 1200 mg dose group in the first cycle. When administered for 21 days, the majority of receptor occupancy has reached over 90%, suggesting that the drug can maintain saturation until the next administration, ensuring sustained efficacy and supporting the feasibility of administering the drug once every 3 weeks.

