Detection results from other hospitals were also acceptable. Tissue is the first choice for detection samples, if optional blood samples cannot be obtained from tissue, the detection methods can be selected by traditional genetic testing (such as immunohistochemistry, ddPCR, Arms-PCR, etc.) or high-throughput sequencing.

1. At least one measurable lesion according to Response Evaluation Criteria in Solid Tumors (RECIST) version 1.1, without prior radiotherapy in the past three months;
2. Predicted life expectancy of ≥3 months; Eastern Cooperative Oncology Group (ECOG) performance status (PS) of 0-1;
3. Recovered from damages (≤grade 1) associated with other treatments per the CTCAE version 5.0;
4. Adequate function of the important organs as evident by the following criteria:
5. Hemanalysis (no blood transfusion, and without the use of G-CSF or other hematopoietic stimulating factors within 14 days):
6. Hemoglobin (HB) ≥80g/L;
7. Absolute neutrophil count (ANC) ≥1.5×10^9/L;
8. Platelets (PLT) ≥75×10^9/L;
9. Biochemistry:
10. Total bilirubin (TBIL) ≤upper limit of normal value (ULN);
11. ALT and AST ≤1.5×ULN;
12. Creatinine (Cr) ≤1.5×ULN or creatinine clearance rate (CCr) ≥60 mL/min;
13. Urinary protein <++;
14. Coagulation function: INR and APTT ≤1.5×ULN;
15. Doppler ultrasound assessment: left ventricular ejection fraction (LVEF) ≥50%;
16. Women of childbearing potential must have adopted contraception, or have a negative serum and urine pregnancy test within 7 days before the study enrollment; women of childbearing potential and men must agree to contraception for the duration of study treatment and 8 weeks after the last dose of study treatment, or have been of sterilization;
17. Be willing and able to provide written informed consent for the trial, and comply with all aspects of the protocol.
    1. Exclusion criteria

The exclusion criteria were:

1. Patients with a history of malignant tumors within 5 years before the start of treatment except for patients with cured orthotopic cervical cancer, cutaneous basal cell carcinoma, cutaneous squamous cell carcinoma, or superficial bladder cancer (Ta [non-invasive cancer], Tis [orthotopic cancer], T1 [superficially invasive]);
2. Central squamous cell lung cancer or squamous cell lung cancer with a significant pulmonary cavity;
3. Have received >1 systemic chemotherapy during previous lines of treatment (patients with neoadjuvant or adjuvant chemotherapy were allowed to be enrolled);

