**Table 5.5-10 Treatment of immunogenic adverse reactions**

| Immunologically adverse reactions related to the trial drugs | Severity (CTC grade of AEs) | Clinical Management |
| --- | --- | --- |
| Respiratory diseases  (e.g., interstitial pneumonia) | Grade 2 | Suspend treatment and provide symptomatic treatment with glucocorticoids until toxicity subsides to Grade 1 or lower. If toxicity does not recover within 12 weeks after the last administration, treatment should be terminated. |
|  | Grade 3 or worse, or recurrence | Discontinuation of treatment |
| Hepatitis | Grade 2 (3×ULN < ALT or AST < 5×ULN, or 1.5×ULN < total bilirubin < 3×ULN), lasts for more than 5 days | Suspend treatment and provide symptomatic treatment with glucocorticoids until toxicity subsides to Grade 1 or lower. If toxicity does not recover within 12 weeks after the last administration, treatment should be terminated. |
|  | Grade 3 or worse (ALT or AST≥5×ULN, or total bilirubin ≥ 3×ULN） | Discontinuation of treatment |
| Colitis or diarrhea | Grade 2 or 3 | Suspend treatment and provide symptomatic treatment with glucocorticoids until toxicity subsides to Grade 1 or lower. If toxicity does not recover within 12 weeks after the last administration, treatment should be terminated. |
|  | Grade 4 | Discontinuation of treatment |
| Pancreatitis | Grade 2 or 3 pancreatitis  Grade 2 or 3 elevated amylase or lipase | Suspend treatment and provide symptomatic treatment with glucocorticoids until toxicity subsides to Grade 1 or lower. If toxicity does not recover within 12 weeks after the last administration, treatment should be terminated. |
|  | Grade 4 or recurrent pancreatitis | Discontinuation of treatment |
| Endocrine dysfunction | Grade 2 or 3 hypophysitis | Suspend treatment and provide symptomatic treatment with glucocorticoids until toxicity subsides to Grade 1 or lower. If toxicity does not recover within 12 weeks after the last administration, treatment should be terminated. |
|  | Grade 4 hypophysitis | Discontinuation of treatment |
|  | Hyperglycemia of grade 3 or higher (fasting blood-glucose >13.9-27.8 mmol/L） | Suspend treatment and use insulin replacement therapy until blood glucose levels recover to Grade 2 or below and remain stable. |

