AEs of special interest are required to immediately report to the sponsor. Sponsor is responsible for addressing potential new risks of clinical trial by appropriate approaches. Investigators are required to immediately report these following events to the sponsor. In all cases, investigators are required to report the event to the sponsor within 24 hours after learning of the event. Details events (regardless of its causality to study drug) are listed as following:

(1) Pregnancy in female subjects

Female subjects of childbearing potential are recommended to notify the investigators immediately if pregnancy was confirmed during the study or within 6 months after the last dose of study drug. Investigator(s) are required to complete the Clinical Trial Pregnancy Report Form and report to the sponsor or their designated personnel within 24 hours of being informed of a pregnancy occurrence and submit it to the sponsor or their designated personnel. Pregnancy events should not be documented in the electronic Case Report Form (eCRF) of AEs. Investigator should discontinue the treatment for pregnant subjects, provide advices, and discuss the risks of continuing the pregnancy and potential impacts on the fetus. Pregnant subjects will be monitored until the end of pregnancy. Investigator is required to submit the Clinical Trial Pregnancy Report Form when obtaining the latest information on the pregnancy process and outcomes.

(2) Pregnancy in female partner of the male subjects

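### The AE collection rules conflict (at least 21 days, or 28 days or new therapy) and the last scheduled AE check is at day 21, while TQB2450 is still present, so late immune-related events can go uncounted

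*Protocol*

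**What the plan says.** - **Definition of an AE.** Section 6.5, (3) Observation and recording of AEs, counts any medical event from the start of treatment "until 28 days after the end of the study drug or the initiation of other anti-tumor therapy, regardless of its causality to study drugs". It does not say which of the two end points governs. The similar rule for concomitant medication in section 5.6 does: there the earlier of the two applies.
- **Schedule note.** The AE note under Study Procedures, repeated under section 6.1, Stage 2, says: "AEs are recorded from the first dose of the study drug until at least 21 days after the last dose". AEs already open are followed until resolved or stable.
- **Last scheduled assessment.** In both visit tables the AE row is marked up to the end-of-treatment column and is blank afterwards. That column is timed "With 21 days after treatment discontinuation", with a window of ±3 days.
- **Drug persistence.** Section 1.2.3.4 describes TQB2450 "with a half-life of approximately 320 hours for the 1200 mg dose group in the first cycle". On receptor occupancy it says: "When administered for 21 days, the majority of receptor occupancy has reached over 90" per cent, and it uses this to support dosing every three weeks.
- **Endpoint.** The synopsis lists AEs, irAEs and SAEs among the primary safety endpoints.

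**The concern.** A safety endpoint needs one rule for which events count. Here a site that follows the schedule can stop asking about new AEs at about day 21. A site that follows section 6.5 should continue to day 28, but has no visit at which to do so. If the start of another therapy closes the window, a patient who moves quickly to the next line has a shorter observation period than one who does not.

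The ambiguity matters more for an antibody than for a short-lived drug, because exposure continues after dosing stops. Under section 6.5, an irAE that starts after the window, or after new therapy if that ends it, is not an AE at all. It would then be absent from the irAE count even if TQB2450 caused it. The direction of the error is towards too few events.

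**Working it through.** **Step 1: the windows side by side.**

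| Source | End of AE collection |
| --- | --- |
| Schedule note (Study Procedures; section 6.1, Stage 2) | at least 21 days after the last dose |
| Section 6.5, (3) | 28 days after study drug, or start of other anti-tumor therapy |
| Visit tables, AE row | last mark at end of treatment, day 21 ± 3 |

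The latest permitted day for the last visit is 21 + 3 = 24, which is 28 − 24 = 4 days before the section 6.5 window closes. At the nominal day the gap is 7 days.

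**Step 2: how much TQB2450 is left when the windows close.** The half-life is taken as stated; the documents give no concentration data from which to re-derive it. In days it is 320 / 24 = 13.33. With mono-exponential decay, the fraction left after t days is 0.5^(t / 13.33).

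Counted from the last TQB2450 infusion:

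- Day 21: 21 / 13.33 = 1.6 half-lives; 33.6% left.
- Day 28: 28 / 13.33 = 2.1 half-lives; 23.3% left.

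Both windows run from the last study drug, which may be anlotinib on day 14 of the final cycle. Adding 14 days:

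- 21 + 14 = 35 days: 2.6 half-lives; 16.2% left.
- 28 + 14 = 42 days: 3.15 half-lives; 11.3% left.

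Strictly, day 1 to day 14 is 13 elapsed days, which gives 17.1% (34 days) and 11.9% (41 days). The difference is immaterial.

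**Step 3: sensitivity.** The half-life is approximate and comes from cycle 1. For an assumed range of 240 to 400 hours, the remainder is 23.3% to 41.8% at day 21, 14.4% to 31.2% at day 28 and 5.4% to 17.4% at day 42.

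**Step 4: what a longer period would mean.** Five half-lives are 5 × 13.33 = 66.7 days, with 3.1% left. Twelve weeks (84 days) are 84 / 13.33 = 6.3 half-lives, with 1.3% left.

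**The case against.** Several points on the other side stand:

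- Twenty-one days is a floor, so it is compatible with 28. That sites will report different rates is possible but not shown.
- Section 4.5, on subsequent data collection, asks that subjects who discontinue go on being monitored for AEs. The note on concomitant treatment also foresees new treatment-related AEs after discontinuation, and its row is marked in all follow-up columns. So it would be wrong to say that late events are never recorded. But the section 4.5 monitoring applies only where feasible, is waived for several withdrawal reasons and has no end date for new events. Section 5.6 stops concomitant-medication recording at 28 days or new therapy. None of this settles which events count.
- Part of section 6.5 after the SAE definition is not in the text available here. A longer window for serious events may stand there.
- Residual concentration is not a count of missed irAEs.

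A reader might also infer more than the documents support:

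- **That Table 5.5-10 already sets a 12-week horizon for irAEs.** It says: "If toxicity does not recover within 12 weeks after the last administration, treatment should be terminated". This limits how long treatment may stay suspended for an existing toxicity. It is not an observation period for new events.
- **That occupancy stays above 90% at day 28.** The figure is given for day 21 only.
- **That most patients lose the window because they change therapy within days.** No figure supports this.
- **That the contraception and pregnancy periods contradict each other.** One is a duty during "contraception for the duration of study treatment and 8 weeks after the last dose of study treatment"; the other is a duty to report "if pregnancy was confirmed during the study or within 6 months after the last dose of study drug". They serve different purposes and need not be equal.

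**Conclusion.** The conflict between the AE rules is real and should be corrected. The schedule and section 6.5 give different ends of collection, the role of new therapy is unclear, and the last scheduled AE assessment precedes day 28 by 4 to 7 days (from the latest permitted day to the nominal day). By the protocol's own half-life, TQB2450 is still present when the windows close: about 34% and 23% counted from the last infusion, or about 16% and 11% if a day-14 anlotinib capsule is the last dose. If anlotinib continues alone after TQB2450 stops, as section 5.5 allows, the time since TQB2450 is longer and the remainder smaller.

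New irAEs with later onset can therefore go uncounted in a primary safety endpoint. The conclusion is that they can be missed, not that they are. The documents give no rate of late irAEs and no rate of early change of therapy, so the effect on reported incidence has a direction but no size. The percentages rest on the stated cycle-1 half-life and on mono-exponential decay.

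**What to change.** 1. State one AE window, in the same words, in section 6.5 and in both copies of the schedule note. Place the last AE assessment in both visit tables at or after its end.
2. State whether the start of other anti-tumor therapy ends collection of AEs in general, and whether the earlier or the later of the two dates governs.
3. For irAEs, continue to record new-onset events regardless of new therapy, for a stated period counted from the last TQB2450 dose and justified by the half-life: for example, from about five half-lives (67 days) to 12 weeks. Do the same for SAEs unless the protocol already sets a longer window for them.
4. Collect these events at the existing 6- or 8-weekly follow-up contacts, up to the first contact on or after the end of the period. Record the start date of any new therapy so that events can be attributed.

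The cost is protocol and eCRF wording and one AE question at contacts that already take place. The downside is small: some late events will be confounded by next-line therapy and will need a causality judgement. Reporting irAEs separately by onset before and after new therapy would keep this visible.

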**(4) Grading the severity of AEs**

Grading the severity of AEs are assessed by the NCI-CTCAE version 5.0.

**(5) Causality assessment of AEs to drugs**

In this study, the relationship of AEs to TQB2450, anlotinib, and immune response will be assessed.

AEs was categorized as definitely-related, probably-related, possibly-related, possibly-unrelated, and definitely-unrelated.

Investigator(s) are required to assess the causality of AEs to study drugs, according to the following 5 criteria.

(1) Whether the administration time and the suspected AEs exhibit a reasonable relationship;

(2) Whether the suspected AEs fulfill the criteria for the typical reactions of the drug;

(3) Whether the suspected AEs can be explained by the effects of the combined drug, patient’s clinical condition, or other therapies;

(4) Whether the suspected AEs disappear or are mitigated after drug discontinuation;

(5) Whether the same AEs recurred after repetitive administration of the study drugs.

AEs will be calculated as the sum of definitely-related, probably-related, and possibly-related events.

|  | 1 | 2 | 3 | 4 | 5 |
| --- | --- | --- | --- | --- | --- |
| Definite | + | + | - | + | + |
| Probable | + | + | - | + | ? |
| Possible | + | + | ± | ± | ? |
| Unlikely | + | - | ± | ± | ? |
| Unrelated | - | - | + | - | - |

Note: +, Yes; -, No; ±, probably Yes or No; ?, unknown.

- - 1. Serious AEs (SAEs)

SAE is defined as any adverse event that results in any one of the following unanticipated events during the clinical trial period:

- 1. Death and life-threatening events
  2. Events leading to in-patient hospitalization or prolongation of existing hospitalization;
  3. Events causing persistent or severe disability;
  4. Events causing incapacity
  5. Events causing congenital anomalies/birth defects;

Events that should be not classified as SAEs:

1. Hospitalization due to the use of study drugs.
2. Hospitalization due to protocol-specified procedures (e.g., pathological tissue sampling); however, the event leading to in-patient hospitalization or prolongation of existing hospitalization due to these procedures should be classified as SAE;
3. Hospitalization for planned treatment of the disease。

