| Dropout/Removal Criteria | - 1. Participants who do not meet the screening criteria;   2. Participants who are unable to evaluate for efficacy or unable to evaluate safety without receiving 1 dose of the drug;   3. Participants who are treated with chemotherapy, surgical or experimental drugs other than this protocol during the trial;   4. Participant's concurrent use of China Food and Drug Administration (CFDA)-approved modern herbal agents and immunomodulatory agents for the treatment of tumors;   5. Participants who do not follow the dose, method, and course of treatment according to the study protocol. |
| Termination Criteria | Subject must termination the study if the following cases occur (including but certainly not limited to):   - 1. Disease progression (PD) determined according to RECIST 1.1 criteria or considered clinically progressive.   2. Termination of treatment decided by the investigator from the patient's best interests.   3. Occurrence of intolerable adverse reactions or severe adverse events confirmed by the investigator.   4. Patients with poor compliance, using drug amounts outside the range of 80% to 120% of the prescribed dose.   5. Patient withdrawal of informed consent.   6. Initiation of other anti-tumor drug treatments affecting efficacy judgment (such as chemotherapy, targeted therapy, or biologic agents).   7. Unexpected pregnancy. |
| Study Schedule | Estimated date of the start of the study: August 2019  Estimated enrollment date of the last subject: August 2020  Estimated date of the end of the study: August 2021 |
| Study Procedures | TQB2450 plus anlotinib hydrochloride capsules were administered in a 21-day cycle until disease progression or intolerance. |
| Primary effect endpoints | Duration of response (DoR); overall survival (OS); 12-month progression-free survival rate; disease control rate (DCR); objective response rate (ORR) (assessed per RECIST version 1.1 at the following time points: 3 weeks after the first therapy, then every 6 weeks thereafter during therapy.) |
| Primary safety endpoints | Dose-limiting toxicities (DLT); maximum tolerable dose (MTD); vital signs; laboratory index; adverse event (AE); immune-related adverse event (irAE); serious adverse event (SAE) according to NCI CTCAE version 5.0. |

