**8.2.5 Safety analyses**

Safety analysis includes AEs/adverse reactions, serious AEs/adverse reactions, laboratory tests, vital signs, physical examination, ECOG score, 12-lead electrocardiogram.

- - - 1. **AEs**

Medical coding of adverse events/adverse reactions/immune-related adverse events was performed with the use of MedDRA 21.0. The occurrence of adverse events/adverse reactions/immune-related adverse events, serious adverse events/adverse reactions/immune-related adverse events, adverse events/adverse reactions/immune-related adverse events leading to withdrawal, and adverse events/adverse reactions/immune-related adverse events leading to death were summarized, the number and times of occurrence were listed, and the incidence was calculated. The incidence of adverse events/adverse reactions/immune-related adverse events and serious adverse events/adverse reactions were summarized according to system organ classification (SOC) and preferred terminology (PT), and the number and incidence of adverse events/adverse reactions were listed. The association and toxicity grade of AEs/AEs (NCI CTCAE v5.0) were summarized according to SOC and PT, and the number and incidence of AEs/AEs were listed. The list describes the details of the occurrence of each adverse event/adverse reaction for each subject.

- - - 1. **Laboratory tests**

The laboratory tests were classified according to clinical significance, namely normal, abnormal without clinical significance, abnormal with clinical significance or normal and abnormal. The laboratory tests were summarized descriptively by frequency and percentage using cross-classification table.

Lists describe occurrences of normal before treatment but abnormal after treatment, as well as subjects who were abnormal before treatment but worsened after treatment. The mean, standard deviation, median, quartile, minimum and maximum values of routine blood test, blood biochemistry, four coagulation tests, thyroid function, lipase and amylase were listed. The measured values and changes before and after treatment were described. Paired *t* tests were performed when necessary.

Describe the proportion of subjects with abnormal changes who have “abnormal clinical significance”, in which the investigator judges whether the abnormality has clinical significance.

| Type | Tests |
| --- | --- |
| Hemanalysis | WBC, ANC, LYM, RBC, Hb, PLT |

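### The causality item calculates AEs from related events only, against the protocol's own causality-free AE definition; it is probably a mislabelled definition of adverse reactions

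*Protocol*

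**What the plan says.** The relevant statements are all in the protocol.

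- Section 6.5, Adverse events, item (2) defines an AE as an untoward medical occurrence "which does not necessarily have to have a causality to treatment".
- Item (3) sets the recording rule. Medical events within the observation window, "regardless of its causality to study drugs, are considered to be an AE".
- Item (5), on causality, first gives the categories: "AEs was categorized as definitely-related, probably-related, possibly-related, possibly-unrelated, and definitely-unrelated". After the five assessment criteria it gives the counting rule: "AEs will be calculated as the sum of definitely-related, probably-related, and possibly-related events".
- The synopsis names, among the primary safety endpoints, "adverse event (AE); immune-related adverse event (irAE); serious adverse event (SAE) according to NCI CTCAE version 5.0".
- Section 8.2.5 opens with: "Safety analysis includes AEs/adverse reactions, serious AEs/adverse reactions, laboratory tests, vital signs, physical examination, ECOG score, 12-lead electrocardiogram". It goes on: "The incidence of adverse events/adverse reactions/immune-related adverse events and serious adverse events/adverse reactions were summarized". It then states: "The association and toxicity grade of AEs/AEs (NCI CTCAE v5.0) were summarized according to SOC and PT". It also plans a per-subject listing of each event.

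The text available for review contains no sentence that defines adverse reaction.

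**The concern.** Item (5) attaches to the term AE a sum that ordinarily describes an adverse reaction, that is, an event with at least a possible link to treatment. A reader who takes the sentence as the counting rule would exclude events that items (2) and (3) require to be AEs.

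This matters because AE is a primary safety endpoint and the trial is open-label and single-arm (section 3.1). There is no control arm against which to judge background events, and relatedness is an investigator's judgement on five criteria. All-cause incidence is the safety figure that does not depend on that judgement. A related-only reading could also carry into the SAE definition, which is built on the term adverse event, and into the summaries of events leading to withdrawal or death.

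**Working it through.** The plan gives no figure to reproduce. The check compares the statements and then works out what the literal rule would do.

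**1. Can the statements be reconciled?** Let R be the number of events in the three related categories (definitely, probably, possibly) and U the number in the two unrelated ones.
- Items (2) and (3): AE count = R + U.
- Category list in item (5): all five categories are categories of AEs, so again R + U.
- Counting sentence in item (5): AE count = R.

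The last agrees with the others only if U = 0. The rule drops two of the five categories that its own item has just called AEs.

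**2. What happens in section 8.2.5?** In the ordinary sense of the term, adverse reactions number R. Under the counting sentence AEs also number R, so the two quantities coincide. A summary of AEs by association would then have nothing to show in the two unrelated categories. Section 8.2.5 therefore presupposes the definition in items (2) and (3), not the counting sentence.

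**3. Effect on the event count.** Let u = U / (R + U). The literal count is R = (1 − u) × (R + U), so the count is understated by the share u. The documents give no value for u.

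**4. Effect on per-patient incidence.** A patient with at least one related event is still counted. Let N be the patients with any AE and S those whose events were all rated unrelated. Literal incidence falls by the share S/N. Let m be the mean number of events in those S patients and M the mean over all N. Then:
- U ≥ S × m, and R + U = N × M
- so u ≥ (S/N) × (m/M)

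If m is at least M, for instance when patients have similar numbers of events, S/N is u or less. If patients with only unrelated events have fewer events than average, that bound is not guaranteed. In a preferred-term row where each affected patient has one event, m = M = 1 and S = U, so incidence in that row falls by exactly that row's u.

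**The case against.** The best answer is that this is a slip of terminology, not a chosen analysis. The sentence stands in the causality item, directly after the assessment criteria, where a definition of adverse reactions would be expected. Section 8.2.5 seems to contain the same slip: it pairs adverse events with adverse reactions nearly throughout, but writes AEs/AEs in the sentence on association and grade. This explanation is probably right. It does not make the sentence correct: the text says AEs, and no other sentence found gives the sum its proper name.

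A reader might go further and infer that unrelated events disappear, or that the plan abolishes all-cause incidence. The documents do not support that. Item (3) records every event. Section 8.2.5 names AEs and adverse reactions as distinct items, summarises AEs by association, and lists each event per subject. An analyst working from 8.2.5 could report the all-cause rate, and it could be recovered even after a literal reading. Nor does the protocol specify table layouts, so one can say only that the two quantities would coincide, not that particular columns would be identical.

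A reader might also want a percentage for the understatement. None can be drawn from the documents, and a loss in event counts should not be quoted as the same loss in per-patient incidence.

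Finally, no sample size, efficacy estimate or dose-escalation decision uses this sum; dose-limiting toxicity has its own definition in section 6.3. That limits the weight of the point but does not remove it.

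**Conclusion.** The contradiction stands. Item (5) states a counting rule that conflicts with items (2) and (3), with its own category list, and with the separate naming of AEs and adverse reactions in section 8.2.5. The likely cause is a mislabelled definition of adverse reactions.

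The consequence is conditional. Only if the sentence is applied literally does the AE event count omit the possibly-unrelated and definitely-unrelated events. Per-patient incidence would then be understated by that share or less, provided patients with only unrelated events do not have fewer events than average. The size cannot be stated because the documents do not give the share. Data collection is unaffected.

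The sentence should be corrected because it concerns a primary safety endpoint and would give a wrong result if followed.

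**What to change.** Replace the counting sentence in section 6.5, Adverse events, item (5) with:

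*Adverse reactions (treatment-related AEs) are the sum of definitely-, probably- and possibly-related events; AE incidence includes all events regardless of causality.*

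In section 8.2.5, change AEs/AEs in the sentences on association and toxicity grade to adverse events/adverse reactions, so that the pair reads the same throughout.

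This brings item (5) into line with items (2) and (3) and gives section 8.2.5 the definition of adverse reaction that it relies on. It needs no new data, visits or patients and touches no dose or treatment rule. The cost is the wording change and its filing as a protocol modification.
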